### Measures

The goal of the study is to demonstrate impact of a PC program implementation for NH residents with moderate-to-advanced cognitive impairment using several validated measures. The EOLD-CAD (End of Life Dementia – Comfort Assessment in Dying) scale is designed for proxy report of symptoms, including pain, shortness of breath, restlessness, and calm. It has been used in studies evaluating care for residents with advanced dementia in NHs and as an outcome measure in PC studies [29–34]. The EOLD-SM (End of Life Dementia – Symptom Management), quantifies the frequency of nine signs or symptoms, including pain, shortness of breath, depression, fear, anxiety, and agitation [31]. For the UPLIFT-AD study, the outcome assessment instrument includes the modified EOLD-CAD and EOLD-SM items and measures proxy report (for both staff assessments and surrogate decision-maker/family assessments) of the frequency and intensity of symptoms over the past month. In addition, family respondents are asked questions from the EOLD-SWC (End of Life Dementia – Satisfaction with Care) scale [31, 35]. Table 3 (pp. 25–26) summarizes information about all study measures.

**Table 3 Tab3:** Key study measures for the UPLIFT-AD trial by study aim

Measure	Construct	Description	Properties (subscales & reliability coefficients if appropriate)	UPLIFT Data Source(s)	UPLIFT Aim	Data Collection Periods
EOLD-CAD	Intensity of symptoms and conditions	*Items*: 14 *Recall*: Past 30 days *Response options*: 3-point ranging from “not at all intense” to “very intense”^a^	Full scale [36]: α = .85 Subscales [36]: Physical Distress: α = .74 Emotional Distress: α = .82 Well Being: α = .80 Dying Symptoms: α = .70	NH Staff Family	Aim 1	T1, T2, T3, T4
EOLD-SM	Frequency of physical and emotional symptoms	*Items*: 9 *Recall*: Past 30 days *Response options*: 6-point ranging from “never” to “every day”	Full scale [36]: α = .78 Subscales [36]: Psychological Symptoms: α = .81 Physical Symptoms: α = .47^b^	NH Staff Family	Aim 1	T1, T2, T3, T4
EOLD-SWC	Satisfaction with care	*Items*: 10 *Recall*: Past 30 days *Response options*: 4-point ranging from “strongly agree” to “strongly disagree”	Full scale [36]: α = .90 Subscales: [None]	Family	Aim 1	T1, T2, T3, T4
Palliative Care Screen	Assessment of resident PC needs; acuity assessment	*Items*: 6 *Recall*: Present *Response options*: Yes/No	N/A; created by the UPLIFT research team; items cover non-concordant goals of care; lack of ACP documentation; hospitalization; unmanaged symptoms; polypharmacy; complex care	PC Leads	Aim 2	Within 1 month of UPLIFT initiation; then as needed
Fidelity Checklist	UPLIFT Implementation Tracking	5 domains	N/A; created by the UPLIFT research team; domains include referrals/consultations; hospitalizations; deaths; adverse events; change in PC needs	PC Leads and/or PC Consultants	Aim 2	At least monthly during UPLIFT implementation
Debriefing Interviews	Qualitative perceptions of implementation	Semi-structured interviews	N/A; created by the UPLIFT research team; includes perceptions of training, areas for improvement, sustainability	PC Leads	Aim 2	T3
Palliative Care Survey	Knowledge of and engagement in PC practices	*Items*: 51 *Recall*: Varied *Response options*: Varied	Subscales [26]: PC Practice Subscale: α = .75 PC Knowledge Subscale: α = .81	NH Staff	Aim 3	T1, T2

“Family” respondents are broadly defined as the person responsible for making health-related decisions on behalf of the UPLIFT resident, which occasionally includes guardians, or close friends

T1 = Baseline; T2 = 6 months post-UPLIFT initiation; T3 = 1 year post-UPLIFT initiation; T4 = 1.5 years post-UPLIFT initiation (i.e., 6 months after UPLIFT discontinuation)

*NH* Nursing home, *PC* Palliative care, *ACP* Advance Care Planning, *EOLD-CAD* End of Life Dementia – Comfort Assessment in Dying scale, *EOLD-SM* End of Life Dementia—Symptom Management scale, *EOLD-SWC* (End of Life Dementia – Satisfaction with Care) scale

^a^The original EOLD-CAD response option indicating “a lot intense” was modified to instead read “very intense” during pilot testing of study measures during

^b^Due to the low correlation among Physical Symptom items (*n* = 3), the scale creators suggest assessing these three items independently

In order to evaluate the impact on the education program included in UPLIFT-AD and the diffusion of knowledge from the presence of a PC consult program, a Palliative Care Survey is conducted in the NHs at baseline and six months post-implementation. Multiple frontline clinical staff are asked to complete the survey. The Palliative Care Survey is a validated instrument to measure NH staff knowledge, attitudes, and practices regarding PC [25–27]. It includes patient vignettes and questions regarding frequency of key behaviors, such as family communication.

### Statistical analyses

The primary outcome of the trial is the EOLD-CAD as assessed by NH staff. Family-reported symptom data will be analyzed separately and compared to staff measures for agreement. Analysis will be carried out in an intention-to-treat framework [37]. Consistent with the analysis of stepped wedge trials, we will implement the analysis in mixed-effect models [38]. A key independent variable to be included is the binary indicator for treatment periods (0 = pre-intervention, 1 = post-intervention). Other resident characteristics, such as age, sex, race, and degree of cognitive and functional impairment, will be modeled as covariates. As in trials with a stepped wedge design, all time-invariant resident and facility characteristics will be balanced between the control and intervention periods. Time-varying resident characteristics, however, may be unbalanced. The influences of these factors will be controlled for in the mixed-effects model analysis. Facility-specific random intercepts will be included to accommodate the potential correlations in the outcomes contributed by residents from the same facility. All analyses will be conducted in SAS. The main hypotheses will be tested through PROC MIXED, using a two-sided Wald test. *P* values < 0.05 will be considered statistically significant.

Using the Palliative Care Survey, linear mixed-effects models will be used to compare NH staff PC knowledge and attitudes over time and between conditions. Scores from respondents in the same NH are expected to be correlated; thus, facilities will be included in the model as a random effect. Factors in each model will include respondent and facility characteristics.

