**Methods/design:**

The UPLIFT-AD (Utilizing Palliative Leaders in Facilities to Transform care for people with Alzheimer’s Disease) study is a pragmatic stepped wedge trial in 16 nursing homes in Maryland and Indiana, testing the effectiveness of the intervention while assessing its implementation. The proposed intervention is a palliative care program, including 1) training at least two facility staff as Palliative Care Leads, 2) training for all staff in general principles of palliative care, 3) structured screening for palliative care needs, and 4) on-site specialty palliative care consultations for a one-year intervention period. All residents with at least moderate cognitive impairment, present in the facility for at least 30 days, and not on hospice at baseline are considered eligible. Opt-out consent is obtained from legal decision-makers. Outcome assessments measuring symptoms and quality of care are obtained from staff and family proxy respondents at four time points: pre-implementation (baseline), six months after implementation, at 12 months (conclusion of implementation), and six months after the end of implementation. Palliative care attitudes and practices are assessed through surveys of frontline nursing home staff both pre- and post-implementation. Qualitative and quantitative implementation data, including fidelity assessments and interviews with Palliative Care Leads, are also collected. The study will follow the Declaration of Helsinki.

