### Research ethics

The UPLIFT-AD protocol is approved by the Indiana University Institutional Review Board and follows recommendations for intervention trials according to the SPIRIT checklist [24]. The Research Collaboration Agreement signed by NH administrators and Indiana University includes data privacy and protection provisions. Study data are entered into a secure REDCap database to which only study personnel have access.

Potentially eligible residents are identified by the NH leadership, with eligibility confirmed by research staff. A study information sheet (see Additional File 1) and consent form, with opt-out instructions (see Additional File 2), are mailed to the surrogate decision-maker for each resident. Surrogate decision-makers can opt the resident out of the study via phone, email, or REDCap link. An opt-out consent process for residents has been determined to be appropriate for this minimal-risk study. Consent for treatment must be obtained separately prior to a PC clinical consult taking place.

For outcome assessments, staff members who are familiar with the health and care of the enrolled residents over the past 30 days are identified by supervisors or by asking staff directly which residents they know best. Research staff, presenting the study information sheet (see Additional File 3) then approach staff to enroll them in the study and collect outcome data. A staff member may provide outcome data for more than one resident. Documented verbal consent by the staff member is obtained at the time of enrollment. In addition, research staff enroll surrogate decision-makers, typically family members, for outcome assessments. Surrogate contact information is obtained from the NH. Verbal consent is obtained and documented prior to surrogate participation in outcome assessments.

Frontline clinical staff (e.g., nurses and nursing assistants) are offered the Palliative Care Survey [25–27], which includes a study information sheet that states that completion of the survey indicates consent for data to be analyzed.

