### Inclusion/exclusion criteria

There are three types of research participants in this study: 1) NH residents with indications of cognitive impairment; 2) staff who care for enrolled residents; and 3) surrogate decision-makers (usually family members) of enrolled residents. Inclusion criteria for NH residents are 1) in the facility > 30 days; 2) not currently on Medicare Part A funded rehabilitation care; 3) not receiving hospice services at time of enrollment; and 4) moderate-to-advanced cognitive impairment, with a BIMS score of 12 or less on the most recent assessment prior to enrollment. Inclusion criteria for staff are 1) identified by a supervisor as a person who regularly cares for the resident; 2) employee of the facility; and 3) English-speaking. Inclusion criteria for surrogate decision-makers or family members of residents are 1) familiarity with the care of the resident; and 2) English-speaking. Only one staff member and one surrogate decision-maker provide data for any given resident at each time period; different staff or family members may be enrolled and provide data at later time points for a given resident if needed.

NH staff are recruited to complete Palliative Care Surveys at baseline and six months after implementation. All nursing assistants and licensed nurses (i.e., RNs and LPNs) who interact with UPLIFT-AD residents in the facility are eligible to complete the Palliative Care Survey.

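### The primary mixed model names only a facility random intercept although the same residents are rated at up to four time points, so its model-based standard error and p-value are not valid as written

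*Protocol article*

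**What the plan says.** All of the following is from the protocol article.

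- **Outcome** (Statistical analyses): "The primary outcome of the trial is the EOLD-CAD as assessed by NH staff".
- **Treatment variable** (Statistical analyses): the key regressor is a "binary indicator for treatment periods (0 = pre-intervention, 1 = post-intervention".
- **Random effects** (Statistical analyses): "Facility-specific random intercepts will be included to accommodate the potential correlations in the outcomes contributed by residents from the same facility". No resident effect, repeated-measures covariance, facility-by-time effect or rater effect is named.
- **Test** (Statistical analyses): "The main hypotheses will be tested through PROC MIXED, using a two-sided Wald test", and P "values < 0.05 will be considered statistically significant".
- **Repeated assessment** (abstract, Methods/design): outcomes are obtained "at four time points: pre-implementation (baseline), six months after implementation, at 12 months (conclusion of implementation), and six months after the end of implementation". Table 3 lists EOLD-CAD at T1 to T4.
- **Raters**: one staff member rates a given resident at each time point, but "different staff or family members may be enrolled and provide data at later time points for a given resident if needed" (Inclusion/exclusion criteria). Also, "A staff member may provide outcome data for more than one resident" (Research ethics).

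**The concern.** The stated random effect deals with one source of dependence, residents sharing a facility. The design creates at least two more.

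1. **Same resident, several rounds.** Treatment switches from 0 to 1 within each resident who is followed past baseline. With only a facility intercept, the model gives a resident's T1 and T2 scores the same correlation as scores from two different residents. Stable differences between residents, which partly cancel in a pre/post contrast, are counted as noise. The reported standard error is then too large.

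2. **Same facility, different rounds.** T1 to T4 spans at least a year and a half. A lone facility intercept makes two residents rated in one round exactly as correlated as two rated 18 months apart. The Discussion reports COVID-19 outbreaks, staff turnover and changes of ownership, any of which can shift a whole facility's scores between rounds. Such shifts do not cancel in a pre/post contrast. Ignoring them makes the reported standard error too small.

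Shared raters who change between rounds act like the second source on a smaller scale. At stake are the standard error, confidence interval and type I error of the trial's primary test.

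**Working it through.** **The plan's own figure.** The Power calculation section gives more than 90% power for 0.5 SD with 640 residents, 16 facilities and ICC 0.1 to 0.2. I used the Hussey–Hughes variance with 16 facilities, 4 sequences, 5 periods (assumed) and 8 residents per facility-period (640 observations).

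- ICC 0.1: variance = 16 × 0.1125 × (0.1125 + 5 × 0.1) / (160 × 0.1125 + 480 × 0.1) = 1.1025 / 66 = 0.0167, SE 0.129. Power = Φ(0.5/0.129 − 1.96) = 97.2%.
- ICC 0.2: SE 0.125, power 97.9%.

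The stated figure is reproduced.

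**Inputs for the check.** From the article: 16 facilities, 40 residents each at baseline, four rounds, ICC 0.1 to 0.2, two-sided 0.05. Assumed, because the article gives no values:
- residents rated per facility of 40, 31, 26 and 22 over T1 to T4, with monotone drop-out;
- indicator 0 at T1 and 1 at T2 to T4;
- resident correlation ρ, the share of within-facility variance that stays with the resident;
- cluster autocorrelation (CAC), the between-round correlation in a facility divided by the within-round correlation.

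Total variance is 1 and covariates are ignored.

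**Formulas.** Every facility has the same layout, so the as-written estimate without calendar effects is the post mean minus the pre mean, averaged over facilities. Let w = 1 − ICC and γ = ICC × (1 − CAC).

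- A = 1/40 + 1/79 = 0.03766, where 79 = 31 + 26 + 22.
- B = sum over residents of (k/79 − 1/40)², where k is the number of post ratings: 22 residents have 3, 4 have 2, 5 have 1 and 9 have 0. B = 0.01009.
- C = 1 + (31² + 26² + 22²)/79² = 1.340.
- True variance = [(1 − ρ)wA + ρwB + γC] / 16.
- Model variance = sA/16, where s is the within-facility mean square that the model takes as residual: s = (1 − ρ)w + 0.979ρw + 0.743γ.
- Type I error = 2[1 − Φ(1.96 × model SE / true SE)].

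**One case in full** (ICC 0.1, ρ 0.5, CAC 0.8, so w = 0.9 and γ = 0.02). True variance = (0.01695 + 0.00454 + 0.02680)/16 = 0.00302, SE 0.0549. s = 0.450 + 0.440 + 0.015 = 0.905; model variance = 0.905 × 0.03766/16 = 0.00213, SE 0.0462. Ratio 0.84, type I error 10.0%.

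| ICC | CAC | ρ | Model SE | True SE | Ratio | Type I error |
|---|---|---|---|---|---|---|
| 0.1 | 1 | 0 | 0.0460 | 0.0460 | 1.00 | 5.0% |
| 0.1 | 1 | 0.3 | 0.0459 | 0.0407 | 1.13 | 2.7% |
| 0.1 | 1 | 0.5 | 0.0458 | 0.0366 | 1.25 | 1.4% |
| 0.1 | 1 | 0.7 | 0.0457 | 0.0321 | 1.42 | 0.5% |
| 0.1 | 0.95 | 0.5 | 0.0459 | 0.0420 | 1.09 | 3.2% |
| 0.1 | 0.9 | 0.5 | 0.0460 | 0.0467 | 0.98 | 5.4% |
| 0.1 | 0.8 | 0.5 | 0.0462 | 0.0549 | 0.84 | 10.0% |
| 0.2 | 0.95 | 0.5 | 0.0434 | 0.0451 | 0.96 | 5.9% |
| 0.2 | 0.8 | 0.5 | 0.0440 | 0.0674 | 0.65 | 20.1% |

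The first row confirms that the stated model is correct when neither extra source exists. With calendar-period effects added (waves assumed six months apart), the cases at ρ 0.5 with ICC 0.1/CAC 1, ICC 0.1/CAC 0.8 and ICC 0.2/CAC 0.8 give about 1%, 8% and 17%.

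**Raters.** Assume a rater variance of 0.1, ten raters per facility-round, new raters each round, ICC 0.1 and CAC 1. With no resident correlation, the true SE is 0.0522 against a model SE of 0.0460, type I error 8.4%. With ρ = 0.5 the figures are 0.0451 and 0.0458, type I error 4.7%. With 8 residents per rater instead of 4, and ρ = 0.5, the error is about 8% to 11% over ICC 0.1 to 0.2. If raters stay the same across rounds, rater variance alone gives about 4%.

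**Power with the full covariance.** The largest SE in the scenarios run was 0.127 SD (calendar effects, ICC 0.2, CAC 0.8, ρ 0.5, rater variance 0.1, 8 residents per rater). Φ(0.5/0.127 − 1.96) is about 97%.

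**The case against.** The strongest reply is that this is a condensed article. It says that facility intercepts will be included; it does not exclude other terms, and an SAP that is not shown may add them. That is fair as to what the final analysis will contain. But the article does not leave the structure open: it names the random effect, its purpose, the procedure and the test, and the resident level is absent from all of these. The point concerns what is fixed there.

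Several stronger readings are tempting and are not supported.

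- **That the test is anti-conservative.** The omission clearest from the text, resident correlation, errs in the safe direction. Inflation needs facility-by-round or rater variation of a size that the article does not give. The 20% case takes the top of the ICC range together with CAC 0.8, whereas the only observed ICC cited is 0.10.
- **That shared raters alone push the error to 10% or more.** This depends on residents per rater, on rater turnover and on leaving out resident correlation. With ten raters per round and resident correlation 0.5 the error is about 5%. The article lets raters change only where needed.
- **That the plan uses no small-sample degrees of freedom.** The article is silent on this. Wald-type tests in PROC MIXED carry denominator degrees of freedom, and Kenward–Roger is itself a Wald-type test.
- **That the power claim fails.** It does not, as shown above.

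**Conclusion.** The point holds as a defect in the stated covariance structure. Followed as written, the model's standard error is correct only if residents have no persistent level of their own and facilities do not drift between rounds, or if the two errors happen to cancel. In the cases tabulated with at least one of these sources present, the nominal 5% test runs anywhere from about 0.5% to 20%:

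- resident correlation of 0.3 to 0.7 alone gives about 0.5% to 3%, with lost precision;
- resident correlation 0.5 with cluster autocorrelation 0.8 gives about 10% (ICC 0.1) and 20% (ICC 0.2);
- ICC 0.1 with cluster autocorrelation 0.9 gives about 5%, by cancellation.

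Resident correlation, cluster autocorrelation, rater variance and retention are all assumptions. The net direction cannot be determined from the documents, so a reader should not conclude that the trial will produce too many false positives, or too few. The conclusion is that the error rate of the primary test is not controlled by the analysis as described. The statement of more than 90% power for 0.5 SD is unaffected.

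**What to change.** In the primary model, and in the models for the family-reported scales:

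1. Add a random intercept for resident within facility, or an equivalent REPEATED covariance over T1 to T4.
2. Add a facility-by-time random effect.
3. State a degrees-of-freedom method suited to 16 facilities, for example DDFM=KR.
4. For staff-rated outcomes, fit a staff-rater random effect as a sensitivity analysis, or include it in the main model if rater identifiers are recorded and the model is estimable.

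These choices should be fixed before outcome data are analysed. The cost is SAP wording, a longer model run and possibly a wider confidence interval. No new data are needed.

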### Power calculation and sample size

With a projected sample size of 640 UPLIFT-AD residents (an average of 40 enrolled residents per facility), we have > 90% power to detect an intervention effect size of 0.5 standard deviations in the primary outcome, EOL-CAD, when the level of intraclass correlation is between 0.1 and 0.2. Van der Maaden’s recent trial observed an ICC of 0.10 [39]. An effect size of 0.5 typically indicates a medium level of intervention effect [40, 41]. For the outcomes of interest,

Volicer and colleagues reported that the standard deviations of the EOLD-CAD and EOLD-SWC from a similar population were ~ 6 [36]. An effect size of 0.5, therefore, assures ample power for detecting a change of 3 points in EOLD-CAD and EOLD-SWC. Similarly, for the Palliative Care Survey completed by NH staff, the study will also have sufficient power to detect a difference of 0.5 standard deviations [26]. Based on our experience, intervention effects of such magnitudes are of clinical significance.

### Implementation evaluation

Within the RE-AIM [42–44] framework, Reach is defined as the proportion of the target population who participate in the intervention. We will assess the percentage of eligible residents with dementia who receive at least one PC assessment. We anticipate that > 75% of enrolled residents will receive a PC assessment. Effectiveness will be assessed by the primary study outcome. Adoption is defined as the degree to which PC Leads implement the program as intended, as assessed from regularly scheduled check-in reports and qualitatively through PC Lead interview data. Implementation will be tracked by ongoing fidelity monitoring and assessment of clinical notes from PC consultations. Maintenance includes ongoing contact with the research team to encourage adherence to the protocol and to maintain productive relationships with PC consultants during the implementation period.

## Discussion

The UPLIFT-AD intervention is designed to address the challenge of meeting the PC needs of residents in NHs in a pragmatic fashion, with the goal of creating and testing a replicable model of care. The UPLIFT-AD trial began recruitment of NHs in mid-2021. NH recruitment and participant recruitment is ongoing and final data collection is anticipated to occur in early 2025.

The launch and early implementation of this project included multiple challenges. Some of these challenges were anticipated when the project was originally conceptualized, such as NH staff turnover. To mitigate interruptions in the intervention due to turnover, we are recruiting and training a minimum of two PC Leads at each site and offering ongoing access to staff PC education. Given the long experience of the research team in working in the NH clinical setting, another challenge that was anticipated is the difficulty in integrating new clinical providers into this complex, reactive healthcare setting. An explicit aspect of the PC Lead role is to serve as an anchor point for the external PC consultants; they support the implementation of recommendations and communicate information across clinical providers and other care staff. The PC Consultants also invest time building relationships with the clinical leadership (e.g. primary care providers) in the facility and elicit communication preferences.

Other challenges were not anticipated when the study was designed, such as COVID-19 outbreaks and the degree of instability in the industry, including shifts in corporate ownership. This has caused difficulties in recruiting facilities. NH leaders, while generally supportive of PC and the support it may offer residents, were unable to commit to a project with an uncertain start date, thus we were unable to randomize all facilities in terms of start dates in the original stepped wedge design. Instead of having all 16 NHs recruited and randomized at the start of the study as planned, we assigned the sequence of intervention rollout according to the availability of NHs that expressed interest in participating. This accommodation was considered necessary to address the preferences of the NH providers.

This article describes the protocol for implementing a multi-component PC model in a stepped wedge trial in 16 NHs. Interventions and programs designed to improve the care experience of residents all involve adoption of new or refinement of existing clinical practices. A large review describing NH interventions that were designed to change staff practices identified that interventions with theory-based implementation strategies, designed to address common barriers, had stronger impact [45]. The UPLIFT-AD intervention, led by a team with deep experience in both clinical practice and research in the NH setting, includes multiple flexible implementation elements. If successful, UPLIFT-AD may serve as a standard for PC delivery in NHs.

